### Objectives {7}

This manuscript is a detailed description of the study design and methodology of the randomized controlled trial “The CRC Frailty study”. The study aims to evaluate if the addition of CGA and care prior to colorectal surgery in the frail elderly could improve postoperative outcome, compared to frail elderly receiving standard care, both within an enhanced recovery after surgery (ERAS) setting.

The primary hypothesis of the RCT is that preoperative intervention with CGA and care, in addition to the conventional pre-, peri-, and postoperative care, will improve 90-day mortality rates after surgery for colon and rectal cancer. Based on previous studies and data from the Swedish Colorectal Cancer Registry (SCRCR) (adjusted for age and ASA classification) [12–14, 35], we know that this group of patients suffer higher mortality rates than younger, robust patients, thus making it highly interesting to investigate whether our intervention can improve this hard endpoint. The secondary hypothesis is that the intervention will improve outcome and recovery after surgery measured as complications, specified in the secondary endpoints stated below.

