### Intervention description {11a}

#### Standard protocol

Standard protocol for the treatment of colorectal cancer patients is according to best known practice, based on Swedish colorectal guidelines and within an ERAS setting. The preoperative investigation includes colonoscopy with biopsy (if possible), sometimes in combination with CT colonography, CT scans of the thorax and abdomen and in the case of rectal cancer also MRI of the lower abdomen. Each patient is thereafter discussed at a multidisciplinary team conference (MDT) and given a recommendation of treatment based on the endoscopic, radiologic and histopathologic findings. If the recommendation is surgery with a curative intent, this is scheduled within 4 weeks from their first visit at the outpatient clinic. According to the Swedish standardized referral pathways for colorectal cancer [36], the aim is to proceed from suspicion of colorectal cancer to surgery within 39 days. During this time, each patient has another appointment with the surgeon, followed by a pre-anaesthetic assessment by an anaesthesiologist. Interdisciplinary referrals (e.g. to cardiologist, lung physician) and/or further radiologic and physiologic examinations (e.g. UCG, spirometry) are made if deemed necessary through these evaluations. The patients are admitted to the surgical ward on the day before the planned surgery or the day of the operation. All surgical specimens are analysed by a pathologist and the postoperative TNM stage is determined. When the postoperative staging is completed, all patients are again discussed at MDT and a recommendation is made regarding following oncological treatment and future follow-up. All patients have a scheduled visit at the outpatient clinic in approximately 2 months post-surgery, to receive pTNM information, evaluate the postoperative recovery and plan for any following treatment and follow-up.

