**Fig. 1 Fig1:**
[figure not shown]
Description of the CGA and care concept in the study

**Table 1 Tab1:** Screening instruments and assessments used for the intervention group, at baseline, at post-op visit (approximately 2 months post-op) and at 12 months post-op

Health care professional	Outcome and instruments	Other evaluations	Time of measurements
Internal medicine physician	- **Comorbidity**—*Charlson comorbidity index (CCI)* - **Medication safety**	- Review of SMA and current medications - Overall assessment of physiological status (including blood pressure and ECG)	**CCI** - Baseline - Post-op visit
Study nurse	- **Frailty**—*CFS-9* - **HRQoL**—*EQ-5D-5L* - **Cognition**—*MMSE* - **Medication safety**—*SMA and list of medications* -** Complications**—*Clavien-Dindo scale*		**CFS-9** - Baseline - Post-op visit **EQ-5D-5L** - Baseline - Post-op visit - 12 months post-op **MMSE** - Baseline **SMA** and list of medications - Baseline - Post-op visit **ADL** - Post-op visit **Complications** - Post-op visit
Physiotherapist	- **Dependence**—*ADL-step* - **Physical function** *hand grip strength (HGS) and six-minute walk test (6MWT)*	Overall assessment of the physical status	**ADL** - Baseline **HGS** - Baseline **6MWT** - Baseline
Dietician	- **Nutrition**—*MNA-SF*	Overall assessment of the nutritional status	**MNA-SF** - Baseline - Day of/day before surgery

All patients in the intervention group are discussed weekly in a group consisting of at least one representative from each profession. During these weekly meetings, the expected benefit of the interventions is weighed against the risk of delaying the surgery in each individual case. Adherence to the individually prescribed recommendations is evaluated and when the intervention is completed, or the patient for any given reason is not able to follow the recommendations, the intervention is terminated. To allow the CGA and care intervention to reach as much effect as possible, we have argued the need of, in some cases, allowing the time from diagnosis to surgery to be somewhat prolonged. In general, that time frame is 2–6 weeks but may in the trial setting be extended for up to 8 weeks. The overall objective is though, as in conventional care, to prepare the patient as quickly as possible for surgery without taking unnecessary medical risks. The postoperative phase is similar in both groups (Fig. 1).

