#### Control group

The patients in the control group are assessed using some of the instruments that are used for the intervention group. These measurements are conducted by the regular ward staff (in general a nurse working at the surgery ward/outpatient clinic) at admission to hospital prior to surgery and at the postoperative outpatient visit (Table 2). These extra measurements are the only differences between the control group and patients not included in the trial treated according to standard protocol.

**Table 2 Tab2:** Screening instruments used for the control group, at baseline, at post-op visit (approximately 2 months post-op) and at 12 months post-op

Health care professional	Outcome and instruments	Time of measurements
Ward nurse/nurse at the outpatient clinic	- **Frailty**—*CFS-9* - **HRQoL**—*EQ*-5D-5L - **Cognition**—*MiniMental State Examination (MMSE)* - **Medication safety**—*Safe Medication Assessment (SMA) and list of medications* -** Dependence**—*Activities of Daily Living (ADL-step)* - **Nutrition**—*Mini-Nutritional Assessment-Short Form (MNA-SF)*	**CFS-9** - Baseline - Post-op visit **EQ-5D-5L** - Baseline - Post-op visit - 12 months post-op **MMSE** - Baseline **SMA** and list of medications - Baseline - Post-op visit **ADL** - Baseline - Post-op visit **MNA-SF** - Baseline - Day of/day before surgery
Member of the project steering groups	- **Complications**—*Clavien-Dindo scale* - **Comorbidity**—*Charlson comorbidity index (CCI)*	**Complications** - Post-op visit **CCI** - Baseline - Post-op visit

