### Outcomes {12}

Primary endpoint:All-cause 90-day mortality

Secondary endpoints:Length of hospital stay and the total number of hospital days within 3 months after dischargeDischarge destination (home or nursing facility) and use of home help services30-day readmission ratesADL performance at follow-up in comparison to baselineSafe medication assessment at follow-up in comparison to baseline, adverse drug reactions (ADRs), underuse of evidence-based drug therapy and effects of inappropriate medications (analysed retrospectively)CFS-9 score at follow-up in comparison to baselinePostoperative complications according to the Clavien-Dindo scale at follow-upHealth-related quality of life (HRQoL) at follow-up in comparison to baselineCost-effectiveness based on mortality and HRQoL data (quality-adjusted life years [QALYs]) and costs of hospital care and primary care at baseline, 2 and 12 months post-surgeryAll-cause 1-year mortality

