#### Outcomes and measurements

*Hospital stays and discharge destination*, data regarding the length of hospital stay, total number of hospital days within 3 months after discharge, discharge destination and use of home help services and 30-day readmission rates for all participants is collected from patient medical records.*Dependence*, evaluation of the level of independence/dependence in an elderly individual is of great importance for example when establishing the need of home help services or other assistance. This is assessed using the activities of daily living (ADL)-staircase, which is a validated and commonly used instrument. The screening results in a score from 0 to 9, where 0 is completely independent and 9 is completely dependent [42, 43]. A clinically significant change is defined as a change of minimum 1 step in any direction on the ADL-staircase. ADL-function is assessed at baseline and at post-op visit (approximately 2 months post-surgery). The patients are assessed by a physiotherapist or a study nurse at baseline and follow-up.*Physical function*, the physiotherapists are also using hand grip strength (HGS) and six-minute walk test (6MWT) to make an overall assessment of the patient’s physical status to establish individual recommendations on physical activity and exercise. Both HGS and 6MWT have previously been used in assessments of frail elderly patients [44, 45]. The tests are performed at baseline and not at follow-up and are only conducted on patients in the intervention group as part of the CGA and care intervention.*Nutrition*, malnutrition is common in the elderly population, especially if hospitalized, living in nursing facility or having home help services. Malnutrition is often unrecognized if not specifically targeted. The Mini-Nutritional Assessment-Short Form (MNA-SF) is a validated instrument for nutritional screening in frail elderly individuals. It renders a score which places the patients in one of three groups: normal nutritional status, at risk of malnutrition or malnourished [46, 47]. A clinically significant change is defined as a change in group classification. The patients in the intervention group are screened by a dietician at baseline and by a ward nurse or a dietician at the day of/day before surgery. The patients in the control group are screened by a study nurse at both measurements.*Medication safety*, polypharmacy and the use of potentially inappropriate medications is a growing issue in the elderly population. There is often a need of reviewing and altering an elderly individual’s prescribed medications to reduce the risk of adverse drug reactions and to enable beneficial pharmacological treatments [48–50]. The Safe Medication Assessment (SMA), including a review of the current list of medications [51], is used as a basis for assessing the individual patient’s medications in the trial. The instrument renders a score of 0–30, where a higher score indicates a safer treatment. A clinically significant change is defined as a shift of minimum 1 point in either direction. The questionnaire is filled out by a study nurse at baseline and at revisit, for all participants. To identify adverse drug reactions (ADRs), underuse of evidence-based drug therapy and effects of inappropriate medications, scoring scales [49, 50] and clinical judgements based on medical records will be used. These judgements will be retrospectively performed by senior clinicians [52].*Cognition*, a decline in cognitive function is naturally present in the ageing process. Some elderly individuals are experiencing a more pronounced decline, resulting in cognitive impairment or dementia [53]. In the trial, the Mini-Mental State Examination (MMSE) is used as a screening instrument of cognitive function at baseline. It is a validated and reliable assessment tool in screening for cognitive impairment [54]. The screening is performed by a study nurse at baseline for all participants, but the measurement is not done at follow-up.*Frailty* is an independent risk factor of adverse health outcomes and death [21] and also a predictor of increased hospital and health care costs [25]. The degree of frailty is assessed using the Clinical Frailty Scale (CFS-9). The scale ranges from 1, “very fit”, to 9, “terminally ill”. The scale has been validated and proven to be of prognostic value in clinical practice [26, 55, 56]. The estimates are performed by a study nurse at baseline and at revisit, for all participants. A clinically relevant change is defined as a shift of minimum 1 step on the scale. During the initial phase of the trial’s recruitment, a revision of the CFS-9 scale was made, including minor adjustments in the description of the different levels of frailty [57]. Before the updated version (v 2.0) was put into use, a new application to the Swedish Ethical Review Authority was made and was approved on 2021-05-31.*Complications*, postoperative complications are common in elderly patients undergoing colorectal cancer surgery. The complications can result in additional treatments, reoperations, the need of intensive care and death [7, 8]. The Clavien-Dindo classification is a validated and clinically relevant instrument for identifying and grading adverse postoperative events [58]. The postoperative complications are assessed by a physician based on data from the medical records at the time of revisit, for all participants.*Comorbidity*, the patient’s comorbidity is valued through the Charlson comorbidity index (CCI). The instrument is used to assess the total burden of disease and predicts a 10-year mortality for a patient, by using 19 categories of comorbidities. Each condition is given a grade of 1, 2, 3 or 6, based on the risk of death associated with the specific comorbidity [59, 60]. The CCI index estimate will be performed by a physician, based on data from the medical records at baseline and at revisit, for all participants.*Health-related quality of life (HRQoL)*. The instrument EuroQoL-5D-5L (EQ-5D-5L) is used to assess HRQoL in the trial. The tool consists of a questionnaire containing five health dimensions with five response levels and of a visual analogue scale (VAS) where the patient estimates their own overall current health. Each estimated score is represented by an index value which is derived from a pre-defined value set [61, 62]. The assessments are overseen by a study nurse at baseline and at follow-up (2 and 12 months), for all participants.*Health economical calculations*. A health care system perspective will be applied including hospital and primary care. Cost-effectiveness will be analysed based on mortality and HRQoL data (quality-adjusted life years [QALYs]) and costs of hospital care and primary care at baseline, 2 and 12 months post-surgery. An incremental cost-effectiveness ratio (ICER) is calculated regarding cost/QALY gained. QALYs are calculated by multiplying the health state value with the patient’s survival time at 12 months; see also the “Statistical methods for primary and secondary outcomes” section. Data regarding health care costs will be collected and documented for all participants at 2 months and 12 months from baseline. Hospital costs will be obtained from the Swedish Cost-per-Patient database [63] and from hospital-specific administrative systems. Primary health care costs will be collected from the administrative regional health care database in Västra Götalandregion (VEGA) [64] and by the use of models and actual health care contacts.*Mortality*, mortality data will be extracted from patient medical records and cross-checked against the Swedish Population Registry regarding all participants at 2, 3 and 12 months from baseline.

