## Data collection and management

### Plans for assessment and collection of outcomes {18a}

Data regarding the following outcomes: length of hospital stay and total number of hospital days, discharge destination, 30-day readmission rates, ADL performance, safe medication assessment and medication lists, CFS-9 score, postoperative complications and HRQoL are documented on the CRFs at baseline and at the postoperative visit. Data regarding mortality at 3 and 12 months will be collected and documented separately. Data needed for the health economical calculations and cost-effectiveness analysis; health care costs at 2 months and 12 months, HRQoL at baseline, 2 and 12 months follow-up and mortality data at 2 and 12 months will be collected and documented separately. A more detailed description of the data collection and the study instruments, along with their reliability and validity, are found under the “Outcomes {12}” section. The CRFs used for the control versus intervention group, in English versions, are attached to this article as Additional files 3 and 4.

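### The primary endpoint has two incompatible time origins, surgery and baseline; a clock from baseline can favour the arm that waits longer for surgery, and a clock from surgery leaves unoperated patients without a time zero

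*Protocol article*

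**What the plan says.** - Objectives {7}: the hypothesis is that the intervention "will improve 90-day mortality rates after surgery for colon and rectal cancer". The origin is surgery.
- Outcomes {12}: the primary endpoint is "All-cause 90-day mortality", with no origin.
- Outcomes and measurements, mortality paragraph: data are extracted "regarding all participants at 2, 3 and 12 months from baseline". The origin is baseline.
- Plans for assessment and collection of outcomes {18a}: "Data regarding mortality at 3 and 12 months will be collected and documented separately". No origin.

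No section says that baseline means randomisation. For controls, the Control group section (and, in the same terms, Explanation for the choice of comparators {6b}) places the trial measurements "at admission to hospital prior to surgery and at the postoperative outpatient visit". Standard protocol adds: "The patients are admitted to the surgical ward on the day before the planned surgery or the day of the operation". Table 2, however, lists the control nutrition screen once at baseline and again on the day of, or day before, surgery, which implies an earlier baseline.

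In the intervention arm the baseline instruments belong to the intervention day, which is arranged once the patient is randomised and comes before the preoperative programme. The time from diagnosis to surgery, generally 2 to 6 weeks, "may in the trial setting be extended for up to 8 weeks". Standard care schedules surgery within 4 weeks of the first outpatient visit. Statistical methods {20a} and {20c} commit to intention to treat.

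**The concern.** Surgery and baseline are separated by the preoperative interval, and the trial deliberately allows that interval to be longer in one arm. The choice of origin is therefore tied to the allocation.

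If 90 days run from baseline, every week spent preparing for surgery is a week of postoperative risk that the window does not reach. The arm with the longer wait is credited with fewer deaths even if its postoperative survival is identical.

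If 90 days run from surgery, that artefact goes, but a randomised patient who dies waiting or never has the operation has no starting point. Such patients would drop out of an analysis described as intention to treat, and a longer wait gives more room for this.

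This is the sole primary endpoint. At the planned 5% mortality the intervention arm would have about 0.05 × 170 = 8.5 deaths, so a handful of deaths counted differently can move the result.

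**Working it through.** **Plan's own figure.** Sample size {14}: 15% versus 5%, 80% power, alpha 0.05 (two-sided assumed), 5% loss. The two-proportion formula gives 141 per arm, or 160 with continuity correction; 160 / 0.95 = 168.4, so 169. The stated 170 reproduces, and the clock problem does not affect it.

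**Inputs from the protocol.** 15% mortality at 90 days; standard surgery within 28 days of the first visit; up to 56 days from diagnosis in the trial; control admission 0 to 1 day before surgery; 170 × 0.95 = 161.5, so 161 evaluable per arm.

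**Assumptions not in the protocol.** No treatment effect. The same postoperative death curve in both arms, either constant hazard (shape k = 1) or front-loaded (Weibull, k = 0.5). No preoperative deaths at first. Every patient in an arm has the same gap between baseline and surgery.

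**Formula.** With gap g, a 90-day window from baseline contains 90 − g postoperative days:

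F(g) = 1 − exp{ ln(0.85) × [(90 − g)/90]^k }

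Example, k = 1: g = 28 gives 1 − 0.85^(62/90) = 10.6%; g = 42 gives 1 − 0.85^(48/90) = 8.3%; g = 56 gives 1 − 0.85^(34/90) = 6.0%.

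**Results.** The last column is the chance of a significant result favouring the intervention (pooled two-proportion test, two-sided 0.05; nominal value 2.5%).

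| Control gap | Intervention gap | Spurious gain in points, k = 0.5 to k = 1 | False-positive chance |
|---|---|---|---|
| 28 d | 42 d | 1.4 to 2.3 | 6% to 10% |
| 28 d | 56 d | 3.1 to 4.6 | 14% to 33% |
| 1 d | 14 d | 1.1 to 2.0 | 5% to 8% |
| 1 d | 28 d | 2.3 to 4.3 | 9% to 21% |
| 1 d | 42 d | 3.7 to 6.5 | 17% to 45% |
| 1 d | 56 d | 5.4 to 8.9 | 32% to 75% |

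The first two rows are the reading in which both clocks start near randomisation. The others take control baseline as admission.

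**Preoperative deaths.** At 2% per 90 days the gain shrinks but keeps its direction. For 28 versus 42 days it is 1.1 to 2.0 points, for 28 versus 56 days 2.5 to 4.0, and for 1 versus 42 days 2.9 to 5.7.

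**Clock from surgery.** Both arms have g = 0, so 15.0% versus 15.0%: no artefact among operated patients, but no rule for the unoperated.

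**The case against.** **The mortality paragraph may be only an extraction schedule, loosely worded.** The same section times the cost data both after surgery and from baseline, as if the two were interchangeable, and the 2-month visit is plainly postoperative. Death dates followed to 12 months would allow the endpoint to be rebuilt on either clock. This is plausible, but the text does not say it. If accepted, the surgery clock is what remains, with its own gap.

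**Control baseline is not established.** A reader might infer from the Control group section that control follow-up starts at admission while intervention follow-up starts weeks earlier. The documents do not support stating that as fact. The section never calls the admission measurement baseline, Table 2 points to an earlier one, and the participant flowchart is not visible. This objection stands, and the admission-based rows are conditional on that reading. An admission baseline would also omit control deaths before admission while counting intervention deaths before surgery, an opposing distortion.

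**The largest figures are a ceiling.** The 8 weeks run from diagnosis and apply in some cases; the intervention day comes after diagnosis. The Discussion stresses early postoperative mortality, which favours the front-loaded curve. Even a 56-day gap leaves 34 postoperative days in the window, so it is the later deaths that are missed, not the immediate ones. All of this stands.

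**Counting unoperated patients is detail for the analysis plan.** Partly true, and patients with a life expectancy under 6 months or needing urgent surgery are excluded, so such deaths may be few. But an analysis plan cannot settle the matter while the protocol states two origins.

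**Conclusion.** The contradiction is real, sits in the current text and concerns the only primary endpoint. It needs correction before outcome data are compared.

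The direction of the bias from a baseline clock follows from the design: whichever arm is operated on later has fewer postoperative days counted. Its size is not known. With 15% postoperative mortality and no preoperative deaths, it is about 1.4 to 4.6 points if both clocks start near randomisation and surgery falls at day 28 versus day 42 to 56. If control baseline is admission, it is about 1 to 4 points for intervention gaps of 14 to 28 days. Preoperative deaths would reduce these figures.

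A reader might infer that the clock alone could produce nearly the whole 10-point target. The figure of about 9 points, with roughly a 75% chance of a false-positive result, requires control baseline at admission, a 56-day gap for every intervention patient and a constant hazard. The protocol does not support that combination as an expected case, and the point does not rest on it.

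Moving the clock to surgery is not a complete answer, because it leaves some randomised patients undefined under intention to treat.

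**What to change.** - Use one definition in Objectives {7}, Outcomes {12}, the mortality paragraph and the data-collection section {18a}, and delete the reference to baseline for mortality. State the origin of 1-year mortality as well.
- Primary endpoint: death from any cause from randomisation to 90 days after surgery. All randomised patients are in the denominator, deaths before surgery are events, and patients never operated on are followed to a stated fixed day after randomisation.
- Add an intention-to-treat sensitivity analysis of all-cause mortality at one fixed time from randomisation, the same in both arms and long enough to cover the wait plus 90 days. For example, 56 + 90 = 146 days; this is a chosen common cut-off, since the protocol's 8 weeks run from diagnosis.
- Report by arm how many died before surgery or were not operated on.

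**Cost.** Wording only: death dates already come from medical records and the population registry. The downside is that the primary window is somewhat longer in the arm that waits longer, for instance 28 + 90 = 118 days versus 132 to 146 days for waits of 42 to 56 days. That is conservative for the intervention, and the fixed-time analysis checks it.
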